# Targeted heart rate control using the funny current inhibitor ivabradine to reduce morbidity in patients undergoing noncardiac surgery: study protocol for a phase 2a, triple-blind, placebo-controlled randomised trial

**DOI:** 10.1016/j.bjao.2025.100378

**Published:** 2025-02-19

**Keywords:** autonomic nervous system, elective surgical procedures/adverse effects, heart rate, myocardial injury, postoperative complications, prospective studies, vagus nerve

## Abstract

**Background:**

Myocardial injury is strongly associated with excess morbidity and mortality after noncardiac surgery. Higher heart rate may result in perioperative myocardial injury through demand–supply mismatch. Alternatively, higher heart rates may reflect autonomic dysfunction that promotes myocardial injury independently of heart rate. The specific hyperpolarisation-activated, cyclic nucleotide-gated (HCN)-4 (funny) channel inhibitor ivabradine slows the heart rate without altering autonomic control, blood pressure, or myocardial contractility. We hypothesise that individuals with autonomic dysfunction may benefit most from ivabradine reducing heart rate control to minimise myocardial injury-associated morbidity.

**Methods:**

This triple-blind, international, multicentre, randomised, placebo-controlled, parallel group randomised trial will recruit 350 patients, aged ≥55 yr, with cardiovascular risk factors for myocardial injury during elective noncardiac surgery. To achieve the target heart rate <70 beats min^−1^ (sinus rhythm), patients will be randomly allocated in a 1:1 ratio using minimisation and will receive either ivabradine (2.5–7.5 mg) or placebo tablet twice daily, from the morning of surgery for 72 h. High-sensitivity troponin T concentrations will be measured before and up to 72 h after surgery, blinded to participants, clinicians, and investigators. The primary outcome is myocardial injury associated with morbidity within 7 days of randomisation (defined by Postoperative Morbidity Survey). Secondary outcomes include peak troponin concentrations, complications within 30 days, and mortality within 6 months of surgery. Pre-specified analyses will include resting and orthostatic heart rate plus N-terminal prohormone of brain natriuretic peptide concentrations before surgery.

**Conclusions:**

This phase 2b study will explore whether targeted heart rate control reduces morbidity after surgery, using ivabradine to selectively slow the heart rate without altering perioperative autonomic control.

**Clinical trial registration:**

ISRCTN12903789.

At least 300 million surgical operations are estimated to occur each year globally.^1^ Myocardial injury after noncardiac surgery occurs in ∼40% of the highest risk older patients with comorbidity who undergo elective major surgery.^2^ Myocardial injury is defined by prognostically significant elevations in troponin I or T using high-sensitivity troponin assays.^3^ Although the majority of these episodes that occur within 48 h of surgery are asymptomatic, myocardial injury after noncardiac surgery is independently and strongly associated with both short-term morbidity^4^^,^^5^ and longer-term complications including mortality.^6^^,^^7^

Because myocardial injury usually occurs in the absence of chest pain and electro- and/or echocardiographic changes consistent with myocardial infarction,^8^ numerous non-thrombotic mechanisms have been postulated to trigger this sentinel pathophysiological event.^9^ Supply–demand mismatch may occur as a result of haemodynamic lability^10^^,^^11^ and tachycardia,^12^^,^^13^ which increase myocardial oxygen consumption. Higher preoperative heart rates >83 beats min^−1^ are independently associated with myocardial injury.^12^^,^^13^ However, limiting potentially injurious tachycardia with beta-blockers and clonidine resulted in hypotension and ischaemic stroke.^14^ Poise-1 highlighted the hazards of using fixed dose, extended-release beta-blockers without titration or individualised dosing.^15^

Resting heart rate is chiefly determined by vagal (parasympathetic) tone.^16^ The association between perioperative organ injury and higher heart rate may therefore reflect vagal autonomic dysfunction that promotes cardiovascular injury^17^^,^^18^ and multiorgan dysfunction^19^^,^^20^ through inflammatory and cellular protective mechanisms that are independent of heart rate alone.^21^ The Measurement of Exercise Tolerance before Surgery (METS) study investigators reported that delayed heart rate recovery after exercise, an exercise-evoked measure of vagal tone, was independently associated with myocardial injury after noncardiac surgery.^22^ Additional mechanistic work suggests that dynamic perioperative changes in vagal tone are also associated with myocardial injury.^23^ However, the observational design of these studies cannot provide further insights as to whether higher heart rate *per se*, or vagal dysfunction independently of heart rate, underpins the association with higher rates of postoperative morbidity (Fig. 1).

**Fig 1 fig1:**
[figure not shown]
Hypothesis for *the* FUNNY RCT. If elevated heart rate (HR) is a direct mediator of myocardial injury through driving oxygen demand mismatch, the selective inhibition by ivabradine of the funny channel, located in the sino-atrial node (upper yellow area), should reduce myocardial injury and associated morbidity. If elevated heart rate is a biomarker for morbidity, its chief determinant—efferent vagal activity—is reduced. Loss of cardiac vagal function results in reduced cardioprotection (highlighted green area) and additional extracardiac mechanisms that reduce inflammation and confer organ protection in systemic inflammation and ischaemia–reperfusion injury. Cellular protection may be attributable to numerous mechanisms mediated by neurotransmitters released by the vagus nerve, acetylcholine (ACh), and vasoactive intestinal peptide (VIP), dorsal motor nucleus of the vagus nerve (DVMN), nucleus ambiguus (NA).

In contrast to beta-blockers, ivabradine is a specific I(f) current inhibitor that decreases heart rate without altering autonomic control, myocardial contractility, and blood pressure.^24^ These properties have fuelled the use of ivabradine in not only chronic heart failure but also acute cardiac care, where a recent meta-analysis showed that ivabradine effectively decreases heart rate without haemodynamic compromise.^25^ A recent pilot randomised controlled study extended these findings to the first 3 days of the perioperative period, where individualised use of ivabradine was shown to be safe and deliverable.^26^ These properties afford the opportunity to test the hypothesis that individuals with autonomic dysfunction will benefit most from ivabradine reducing heart rate control to minimise myocardial injury-associated morbidity. Ivabradine offers a pharmacological intervention to dissociate heart rate from both established and acquired autonomic dysfunction that may cause organ injury.

In the FUNNY RCT described herein, we hypothesise that targeted heart rate control with ivabradine for the first 72 h of the perioperative period will reduce early myocardial injury and subsequent morbidity within 7 days after surgery. In particular, the protective effect of targeted heart rate control may be more pronounced in participants with poor baseline cardiovascular function (high preoperative N-terminal prohormone of brain natriuretic peptide [NT-proBNP]), vagal autonomic dysfunction (higher preoperative resting heart rate, impaired orthostatic heart rate response), or both.

## Methods and analyses

The protocol was developed in accordance with Standard Protocol Items for Randomized Trials (SPIRIT) recommendations.^27^

### Study design

Multicentre, international, triple-blind, placebo-controlled, parallel group randomised controlled trial.

### Setting

Surgical services of three academic hospitals in Europe. Participant recruitment started in January 2022 and is scheduled to complete in 2025. Recruiting site eligibility criteria include having surgical services performing major elective surgery in adults, the ability to prepare and store frozen plasma/serum samples, and previous participation in interventional research.

### Participants

#### Inclusion criteria

Adults aged ≥55 yr undergoing major non-emergent surgery typically lasting ≥120 min. Participants must have at least one medical risk factor for perioperative myocardial injury (Table 1), which may include a history of hypertension (requiring antihypertensive drug) or hypertension recorded in pre-assessment clinic (BP >140 mm Hg systolic, >90 mm Hg diastolic).

**Table 1 tbl1:** Medical risk factors for the FUNNY randomised controlled trial.

• Coronary artery disease
• Diabetes mellitus requiring oral hypoglycaemic agent, insulin, or both
• Congestive heart failure
• Cerebrovascular accident
• Chronic kidney disease stage 3–5 (eGFR <59 ml min^−1^ 1.73 m^−2^)
• Peripheral arterial disease
• History of hypertension (requiring antihypertensive drug) or hypertension recorded in pre-assessment clinic (BP >140 mm Hg systolic; >90 mm Hg diastolic)

#### Exclusion criteria

Participants are ineligible if they are already participating in a clinical trial of a treatment with a similar biological mechanism (including previous participation in FUNNY), are unable to provide, or refuse, informed consent, or lack capacity to do so. From a cardiovascular perspective, atrial fibrillation (persistent/chronic or paroxysmal) and prior use of ivabradine within 30 days before surgery preclude enrolment. Absolute contraindications to ivabradine are provided in appendix, including a history of hypersensitivity or allergy to ivabradine or any of its excipients. Women of childbearing potential (premenopausal female capable of becoming pregnant unless permanently sterile) cannot participate.

### Enrolment

Coordinated trial leadership at an international, national, and hospital level has ensured local engagement of surgeons, anaesthetists, and intensivists to support screening and trial delivery. Each site has experienced local investigators and research teams, informed by extensive public and patient input to the trial design. Recruitment targets are monitored and actively managed throughout the trial.

Potential participants are screened by research staff after being identified by clinical teams from pre-admission clinic lists and operating lists. Before surgery, potential participants are approached at least 24 h before their operation to discuss the aims, methods, anticipated benefits, and potential harms of the trial, and receive a patient information sheet (Supplementary material). Written informed consent is obtained from each subject on the day of surgery once surgery is confirmed to proceed. The reasons for eligible patients not participating in the trial will be recorded.

### Randomisation

Once surgery on the day is confirmed to proceed, randomisation will occur after the participant has provided informed consent. Participants are randomised in a 1:1 ratio by minimisation with a random component, with group allocation carried out using a central online service. Minimisation variables will be hospital site and surgical procedure (surgery involving the gut or all other surgery). Each participant will be allocated with 80% probability to the group that minimises between-group differences in these factors among all participants recruited to the trial to date, and to the alternative group with 20% probability. The allocation sequence is generated by an automated algorithm and is concealed to all trial investigators. The system for generating the allocation sequence will be bespoke and will be developed in-house. The system will be validated for use by the trial statistician.

### Study interventions

Usual perioperative care will proceed in each centre for participants in this trial. Blood samples will be collected and prepared for serum and plasma before surgery, 24, 48, and 72 h after surgery, between 06:00 and 10:00, before freezing at –80°C, thus maintaining blinding of the primary outcome. Measurement of high-sensitivity troponin in batched frozen samples stored for 928 days does not affect the results providing values indistinguishable from ‘on-demand’ fresh samples (including using these results for the clinical application of rapid diagnostic algorithms).^28^

Before dosing, resting heart rate and orthostatic heart rate changes from sitting to standing are recorded, which quantify cardiac vagal activity.^29^ Participants receive 0–3 tablets that are indistinguishable, being either 2.5 mg of ivabradine or placebo, based on the participant's resting heart rate within 1 h before dosing (Table 2), unless MAP is <60 mm Hg or a new-onset arrhythmia has been recorded. If multiple heart rate measurements have been recorded within 1 h before dosing, the lowest value is taken to determine the dose of the investigational medicinal product (IMP). Dosing is performed by research staff and will occur twice daily from the morning of surgery until the evening of postoperative day 2 (3 days, six administrations). The individualised variable dosage has been shown in our pilot study to achieve the target heart rate of 60–70 beats min^−1^ while decreasing the risk of bradycardia (Table 1).

**Table 2 tbl2:** Protocol for administration of investigational medicinal product, according to heart rate.

Heart rate(beats min^−1^)	Ivabradine or placebo(identical tablets)
<70	Omit
70–84	1 tablet (2.5 mg if ivabradine)
85–100	2 tablets (5 mg if ivabradine)
>100	3 tablets (7.5 mg if ivabradine)

### Blinding and procedures to minimise bias

This is a triple-blind trial, with trial participants, healthcare staff, investigators administering the treatment, and trial statistician all blinded to the treatment group allocation. To maintain blinding, placebo and ivabradine tablets are identical in shape, dimensions, and colour. Each IMP pack allocated to participants is labelled with a unique kit number to maintain blinding. The troponin measurement component of the primary outcome is analysed by individuals masked to the patient treatment allocation and clinical morbidity outcomes. Those assessing clinical outcomes (research associates and principal investigators) are not directly involved in the care of participants and will be unaware of treatment group allocation.

### Data collection

Postoperative outcomes will be recorded by research staff that are unaware of study group allocation on paper case report forms before electronic data entry using a secure web-based data entry platform. Data collection including participant characteristics before surgery is summarised in Supplementary material. Data will be collected from all participants randomised regardless of whether the participant received the intervention according to the trial protocol or not. The occurrence of a specified clinical outcome will be confirmed by the local principal investigator.

### Data monitoring

The sponsor will have oversight of trial conduct at sites, with the Trial Management Group having day-to-day responsibility for quality control and quality assurance of the data collected. An independent Data Monitoring and Ethics Committee (DMEC) and a Trial Steering Committee (TSC) review trial progress at least every 6 months, in accordance with an agreed charter. No formal interim analysis for efficacy is planned. The DMEC will monitor the safety and efficacy of the interventions during the period of recruitment into the trial, and also patient recruitment, data quality, protocol compliance, and loss to follow-up. The TSC will receive recommendations from the DMEC.

### Trial outcomes

#### Primary endpoint

The primary endpoint is a composite of myocardial injury associated with morbidity within 7 days of surgery. Myocardial injury is defined using the VISION study criteria,^3^ provided high-sensitivity troponin T (Elecsys; Roche Diagnostics; Rotkreuz, Switzerland) concentration ≥15 ng L^−1^ on day 1, 2, or 3 after surgery or increase of ≥5 ng L^−1^ from the preoperative value on day 1, 2, or 3 after surgery when the preoperative value is ≥15 ng L^−1^. The Elecsys Troponin T hs assay uses two monoclonal antibodies specifically directed against human cTnT, recognising two epitopes (amino acid positions 125–131, 136–147) located in the central part of the CTnT protein comprising 288 amino acids. Postoperative morbidity is systematically recorded using the Postoperative Morbidity Survey (POMS) on day 3 and day 7 after surgery.^30^

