#### Secondary endpoints

The secondary endpoints include: (1) myocardial injury (as defined earlier); (2) morbidity 2–3 and 6–7 days after surgery, as defined by the POMS; (3) absolute concentrations of serum high-sensitivity troponin T measured on day 1, 2, and 3 after surgery; (4) mortality within 180 days from surgery; and (5) predefined complications at day 30 after surgery graded using the Clavien–Dindo classification.^31^

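### As printed, the myocardial injury rule puts no preoperative condition on the 15 ng/L threshold, so the rise criterion adds no case and a stable or falling raised troponin counts as injury

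*Protocol article*

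**What the plan says.** The Primary endpoint section states that "Myocardial injury is defined using the VISION study criteria" and then writes the rule out. The first alternative, and the start of the second, read "concentration ≥15 ng L^−1^ on day 1, 2, or 3 after surgery or increase of ≥5 ng L^−1^ from the preoperative value". The two are joined at "on day 1, 2, or 3 after surgery or increase of ≥5 ng", with no condition placed before the join. The rest of the second reads "on day 1, 2, or 3 after surgery when the preoperative value is ≥15 ng L^−1". The preoperative condition is attached to the rise only. Nothing limits the first alternative to patients who start below 15 ng/L.

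The rule feeds two endpoints:
- **Primary:** "The primary endpoint is a composite of myocardial injury associated with morbidity within 7 days of surgery", with morbidity taken from the Postoperative Morbidity Survey (POMS).
- **First secondary endpoint:** "1) myocardial injury (as defined earlier", with no morbidity requirement.

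The preoperative value needed for a correct rule is available: "Blood samples will be collected and prepared for serum and plasma before surgery, 24, 48, and 72 h after surgery" (Study interventions).

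On who is enrolled, Inclusion criteria says "Participants must have at least one medical risk factor for perioperative myocardial injury". Table 1 lists chronic kidney disease stage 3–5, congestive heart failure and coronary artery disease among these. The Exclusion criteria section states no exclusion for a raised preoperative troponin. It refers to an appendix, not shown, for further contraindications.

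**The concern.** A rise criterion reserved for patients who start at or above 15 ng/L is useful only if those patients cannot qualify on the absolute threshold. As written they can. A patient whose troponin was already raised before surgery, and did not rise, is therefore classed as having perioperative myocardial injury.

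The trial's hypothesis is that heart rate control over the first 72 h reduces early myocardial injury and the morbidity that follows. For a patient with a stable raised baseline, the injury part of the composite was in effect settled before the first tablet. The composite then reduces largely to whether POMS morbidity occurs. In the secondary injury endpoint no morbidity filter remains.

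The sentence also invites inconsistent programming. One programmer could code it literally. Another could infer a missing condition from the rise clause. The two would produce different primary-endpoint cases from the same data.

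**Working it through.** **1. The logic (no assumption needed).** Let *pre* be the preoperative value and *post* a value on day 1, 2 or 3, in ng/L.
- Limb A: post ≥ 15.
- Limb B: pre ≥ 15 and post − pre ≥ 5.
- If B holds, post ≥ 15 + 5 = 20, so A holds. B is a subset of A, and the rule reduces to A.

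Checking all whole-number pairs with pre from 3 to 200 and post from 3 to 300:
- Pairs meeting B but not A: 0.
- Pairs meeting B, all of which also meet A: the sum over pre = 15 to 200 of (296 − pre) = 35,061.
- Pairs with pre ≥ 15 and a rise below 5 (or a fall) that still count as injury through A: the sum over pre = 15 to 200 of (pre − 10) = 18,135. Examples are 30 to 30 and 40 to 25.

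These counts show how the rule behaves. They are not prevalences.

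**2. The plan's own sample size.** Inputs from the Sample size section: 59% versus 44%, α = 0.05 (two-sided assumed), power 0.80, 173 per arm.

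n per arm = [1.96·√(2·p̄·(1−p̄)) + 0.8416·√(p₁(1−p₁)+p₂(1−p₂))]² / (p₁−p₂)², with p̄ = 0.515

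= [1.96·√0.49955 + 0.8416·√0.4883]² / 0.15² = 173.1

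The stated 173 is reproduced (174 if rounded up), and power at 173 per arm is 0.80. With 1% dropout, 173/0.99 gives 175 per arm and 350 in total. The arithmetic is sound.

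**3. Illustration of dilution.** The documents do not give the share of patients with a raised, non-rising troponin, so the fraction f below is an assumption. Take the planning rates at face value. Let a fraction f stay at 59% in both arms, and let the rest go from 59% to 44%. The ivabradine rate is then 0.59f + 0.44(1−f).

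| f | Placebo | Ivabradine | Relative reduction | Power at 173 per arm | n per arm for 0.80 |
|---|---|---|---|---|---|
| 0 | 0.59 | 0.440 | 25.4% | 0.80 | 174 |
| 0.1 | 0.59 | 0.455 | 22.9% | 0.71 | 214 |
| 0.2 | 0.59 | 0.470 | 20.3% | 0.61 | 271 |
| 0.3 | 0.59 | 0.485 | 17.8% | 0.50 | 353 |

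**4. What correcting the rule would recover in the same illustration.** The fraction f would become non-cases in both arms, giving rates 0.59(1−f) and 0.44(1−f). The absolute difference, 0.15(1−f), is the same as in step 3. At f = 0.2 the rates are 0.472 and 0.352. The relative reduction returns to 25.4%, but power is only 0.62. For f = 0.1 and 0.3, power is 0.71 and 0.53. So the correction restores the meaning of the endpoint and the relative effect. It does not by itself restore 0.80 power.

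**The case against.** **It is probably a drafting slip.** The rule is introduced as the VISION criteria, and the rise clause makes sense only if the first limb was meant for preoperative values below 15 ng/L. The full protocol or analysis plan may state that condition. This is fair, and a reader should not infer that the sponsor deliberately chose to count chronic elevation. But the article writes out an operational rule and that rule is wrong as written. The cited source is not at hand, and no other section supplies the condition. If the unconditional threshold is intended, the rise clause has no function and should go. The sentence needs changing either way.

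**The size is not documented.** This stands. A reader might infer from Table 1 that raised preoperative troponin is common. The article makes it plausible but gives no share. The nearest count is in the Discussion: 992 of 992 + 3343 = 4335 patients (22.9%) in an earlier cohort had elevated troponin within 12 h of surgery. Cohort and window differ, but f = 0.3 for chronic elevation alone would exceed that total.

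**The drug might still help these patients.** This also stands for the primary endpoint. A case needs POMS morbidity as well as injury, and the Discussion proposes heart-rate-related endothelial and inflammatory pathways. It would go too far to say that these primary-endpoint cases cannot be prevented, so step 3, which allows them no benefit, is pessimistic. The argument is stronger for the secondary injury endpoint.

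**Very low power figures do not belong to this point.** A reader might multiply the roughly 40% injury rate in the introduction by 59% to get a 23.6% event rate, for which a 25% reduction (to 17.7%) has about 27% power at 173 per arm. That shortfall comes from a different question about the planning rate and is not caused by the injury rule.

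**Conclusion.** The concern holds on the printed text. The redundancy of the rise criterion is certain and rests on no assumption. It affects who is a case in the primary endpoint and in secondary endpoint 1, so it should be corrected before the data are unblinded.

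The consequence is less certain. Troponin is assayed blinded to allocation and to morbidity, and the same rule applies in both arms. The documents therefore do not support reading this as bias in favour of either arm. The expected effect is dilution and some loss of power, of unknown size. The figures of 0.71, 0.61 and 0.50 hold only for assumed fractions of 10%, 20% and 30% with no treatment benefit in those patients. They measure the shortfall against the plan, not what the correction would win back.

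**What to change.** Before unblinding, restate the rule in the protocol and analysis plan with a preoperative condition on each limb:
- preoperative hs-TnT below 15 ng/L and any day 1–3 value of 15 ng/L or more; or
- preoperative hs-TnT of 15 ng/L or more and a rise of at least 5 ng/L from it on day 1, 2 or 3.

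Use the same definition for the primary endpoint and for secondary endpoint 1.

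**Cost.** No new data are needed: the preoperative sample is already collected, and troponin is measured in stored samples by staff masked to allocation. Two consequences should be accepted openly. Fewer patients will be classed as injured. And the Sample size section describes its 59% using the 15 ng/L threshold alone, so that rate, and the power that depends on it, must be rechecked against the corrected definition. Settling the wording while blinded also avoids a later choice between the two readings that could be challenged as post hoc.
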